**Fig. 1 Fig1:**
[figure not shown]
Flowchart of enrollment, allocation and follow up

Figure 1 outlines the participant flowchart of the study procedure:*Enrollment*: Recruitment will be conducted in the four participating health care centers through printed materials (leaflets and posters) in the health care centers and close community sites (library, pharmacy, market or older persons’ meeting center). Interested individuals will be required to contact their corresponding health care center, where they will first be screened for age (older than 65 years and younger than 81 years) and previous memory training (not having received memory training during the 3 previous years). Those who meet both criteria will be given an appointment to attend an inclusion interview with a study-specific trained physician or nurse at the health care center. Informed consent follows the requirements of the l’Institut d’Investigació en Atenció Primària Jordi Gol (IDIAP Jordi Gol) Clinical Research Ethics Committee. Written consent to participate will be obtained from each person at the beginning of the screening interview. Participants will be selected through the screening interview, which will be used to gather socio-demographic data and enquire about the participant’s medical history and active clinical diagnoses and medications. The GDS-5 and the MMSE will be administered.*Allocation:* After the screening interview, and if the participant is eligible and willing, he or she will be randomly assigned to the EG or to the CG using a closed, opaque envelope with the group information inside. The total time required for screening will be around 30 minutes.*Baseline and follow-up assessments*: Three assessments will be conducted during the study period: at baseline after randomization, between 3 and 4 months post-intervention (short-term post-test), and at 6 months post-intervention (long-term post-test). All three assessments will collect information on the variables detailed in Table 1 and will be conducted by a trained psychologist through in-person interviews in the health care center. Time requirements will be approximately 75 minutes for the baseline assessment and approximately 90 minutes for the follow-up assessments. Standardization of data collection procedures will be ensured through a variety of training and quality-control procedures adhering to CONSORT guidelines for transparent reporting [12]. Data collectors will be blind to the treatment group assignment. All data collectors will participate in an intensive 2-day training workshop that will include information on the study design, recruitment issues, and general research interviewing principles; detailed instruction on the administration of each test or measurement procedure; demonstrations of each test/measurement; and practice sessions with other data collectors. Furthermore, the data collectors will use a user-friendly answer sheet specially designed for the study. All completed sheets will be reviewed by the fieldwork coordinator who, if there are missing data or possible mistakes, will contact the data collectors to resolve any queries.

**Table 1 Tab1:** Tests and other data for the evaluation of the memory training workshop

	ASSESSMENTS			
	Screening	Baseline	Immediate Post-test	Delayed post-test
Medical History	X			
Socio-demographic data	X			
GDS-5	X		X	X
MMSE	X		X	X
RBMT-3		X	X	X
SF-36		X	X	X
Subjective Self-reported Memory Score		X	X	X
MEF		X	X	X
WAIS		X	X	X
TMT		X	X	X
SF-LLFDI		X	X	X

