### Description of the intervention

Once the baseline assessment has been conducted, individuals in the EG will start the multifactorial intervention. The memory training workshop is designed to stop or delay age-related memory losses and promote personal autonomy, thus enhancing mental and physical wellbeing. Specifically, these workshops aim to broaden knowledge on memory function, improve memory processes, and increase self-esteem and quality of life by providing some strategies (i.e., strategies for collecting and coding information) and relational space. The intervention will consist of twelve 90-minute group sessions provided once a week by a psychologist specialized in memory training. The groups will be composed of around 15 people. Each session will have its own objectives, materials, and activities (Table 2). The content of the intervention is based on memory training from different perspectives such as cognitive and emotional aspects and social and individual skills.

**Table 2 Tab2:** Contents of the memory training workshop by session

SESSION	CONTENT
1	Presentation of the workshop: Objectives and Methodology
2	Types of memory I: Explanation of the different types of memory and their role in normal life
3	Types of memory IIa: Strategies for gathering and codifying information.
4	Types of memory IIb: Strategies for selecting and storing information.
5	Types of memory III: Strategies for gathering, codifying, selecting, storing and retrieving information. Importance of the context and the meaning of things. Semantic and episodic memory.
6	Types of memory IV: Strategies for gathering, codifying, selecting, storing and retrieving information. Individual differences.
7	Types of memory V: Strategies for retrieval according to individual profile. Improving self-esteem.
8	Types of memory VI: Strategies for recovering social skills.
9	Personal and social skills
10	New contexts and opportunities. Conceptual maps (physical and mental).
11	Evaluation of the workshop.

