### Main outcomes

*Self-perceived memory* will be measured using a subjective self-reported memory score (from 0 to 10), as well as with the Memory Failures in Everyday life questionnaire (MFE). This questionnaire consists of 28 items and uses a Likert-type scale referring to perception of everyday memory problems [20–22].

*Everyday memory* will be measured using the Rivermead Behavioural Memory Test-3 (RBMT-3) [23]. This cognitive test evaluates different types of memory, such as associative memory, prospective memory, visual memory, topographical memory, and verbal memory. The test provides a General Memory Index and different subtest scales.

*Executive control abilities will be measured in terms of* visual-perceptual ability, working memory and task-switching ability with the Trail Making Test (TMT) [24]. This neuropsychological test is divided into two parts and the score on each part represents the amount of time required to complete the task [25]. Working memory will also be assessed using the digit span scale of the Wechsler Adult Intelligence Scale III (WAIS III).

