## Discussion

### Quality control

Reliability and validity are considered to be the key criteria for assessing the quality of quantitative studies. To assure these qualities, the randomization list of this randomized controlled trial will be computer-generated and will remain concealed until the participants’ assignment to each group. After the informed consent form has been signed, a study entry number will be assigned to each participant. This number will be on the outside of a closed, opaque envelope, which will allocate the participant to either the EG or the CG (single-blind allocation). Allocation concealment will prevent the occurrence of selection bias before the interventions are provided to the participants [36]. In addition, the professionals who will carry out the neurocognitive evaluations (pre-test, short-term post-test and long-term post-test) and the memory training workshop professionals will not be aware of the group to which each participant belongs.

The following procedures will also be used to guarantee the quality of the information. The intervention will be carried out by trained personnel who will follow the same protocol and materials, thus guaranteeing the homogeneity of the intervention. The same will occur with data collection, which will be conducted by specially trained professionals. Data will be collected through a specifically created data-register sheet designed by Teleform® v.10.2 software. This automated software reads scanned questionnaires and performs a validation process of the data with previously established parameters; once the data have been validated, they are entered into a specifically created dataset.

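### Baseline is measured after randomisation with nothing keeping participants unaware of their arm, so a passing reaction to allocation could bias the group-by-time contrast

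*Protocol article*

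**What the plan says.** Under the description of the study (Figure 1), the allocation step comes after the screening interview: "he or she will be randomly assigned to the EG or to the CG using a closed, opaque envelope with the group information inside". The next step is the assessments: "Three assessments will be conducted during the study period: at baseline after randomization". The Quality control section says the randomisation list "will remain concealed until the participants’ assignment to each group".

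Table 1 shows that screening collects only medical history, socio-demographic data, the GDS-5 and the MMSE. The RBMT-3, subjective memory score, MFE, TMT, WAIS digit span, SF-36 and SF-LLFDI all start at the post-randomisation baseline. The workshops come later still: "Once the baseline assessment has been conducted, individuals in the EG will start the multifactorial intervention".

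On blinding, the study description says "Data collectors will be blind to the treatment group assignment", and Quality control extends this to the workshop professionals. No section says the same of participants. The comparator is no workshop, and the limitations paragraph acknowledges that there is no matched active control.

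The Statistical analysis section fits a repeated-measures mixed model to the available data, with group, time (baseline included as a level) and their interaction. The sensitivity analysis fills missing post-test values by LOCF.

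**The concern.** A baseline is useful because allocation cannot have influenced it. Here every main outcome is first measured once the arm has been assigned, and probably once the participant knows it. Disappointment, enthusiasm or a changed view of one's own memory could alter a self-rating, or the effort put into a test, before any training has taken place. Assessor blinding does not prevent this, because the reaction is the participant's own.

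Three things are at stake:

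- **Efficacy contrast.** A between-arm difference at baseline that allocation caused is subtracted from the follow-up difference as if it were chance.
- **Covariate choice.** The plan compares the arms at baseline on outcomes as well as other characteristics, and may adjust for differences found. A difference produced by allocation would be handled as chance imbalance.
- **Losses before baseline.** A participant who withdraws between allocation and baseline has no value on any main outcome. The available-data model has nothing to use, and LOCF has nothing to carry forward.

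**Working it through.** **Order of events.** Taken together, the sections give: screening and consent, envelope, baseline assessment, first workshop session, follow-ups. Nothing inserts a step that keeps the envelope sealed, or the participant uninformed, until baseline is complete.

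**Algebra of the planned contrast.** With baseline as a level of time, the interaction at a follow-up is

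(EG post − CG post) − (EG base − CG base).

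Let *e* be the true training effect, *b* the between-arm shift at baseline caused by knowing the allocation, and *k* the fraction of *b* still present at follow-up. The contrast then estimates

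(*e* + *kb*) − *b* = *e* − (1 − *k*)*b*.

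- *k* = 0 (reaction gone by follow-up): *e* − *b*, a one-for-one shift.
- *k* = 1 (reaction constant): *e*, no bias.

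**Inputs for an illustration.** From Sample size calculation: effect 2 points, SD 4.19, 75 per arm. Assumed, because the document gives no values: within-person correlation 0.6, and *b*. One-tenth of an SD is 0.1 × 4.19 = 0.42, and 0.42 / 2 = 21% of the target effect.

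**Results for the contrast** (difference in mean change between arms, average of 1,000 simulated trials per setting, true effect 2):

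| *b* | Formula, *k* = 0 | Simulated, *k* = 0 | Simulated, *k* = 1 |
|---|---|---|---|
| 0 | 2.00 | 1.99 | 1.97 |
| +0.42 | 1.58 | 1.58 | 2.00 |
| −0.42 | 2.42 | 2.39 | 1.99 |
| +1.0 | 1.00 | 1.01 | 1.99 |

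**Check in a mixed model.** A random-intercept model with group, time and interaction was fitted to one large dataset (3,000 per arm) with *b* = +1 and *k* = 0. It gave 1.01 and 1.02 at the two follow-ups. A second dataset, with random loss of both follow-ups in 40% of controls and 20% of the workshop arm, gave 0.89 and 0.85. Allowing for sampling error, that is again about 1 below the true value.

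**Other analyses at *b* = +1.** With *k* = 0, adjusting follow-up for baseline is only partly affected: 2 − 0.6 × 1 = 1.4 expected, 1.41 simulated. A comparison of follow-up scores alone is unaffected (2.00). With *k* = 1 these two give 2.40 and 2.99, because they absorb the lasting reaction. No choice of analysis removes the problem without knowing *k*.

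**The case against.** The strongest reply is that disclosure before baseline is never stated. The text gives the means of assignment but not the moment when the envelope is opened or the participant is told. Quality control describes the envelope as one "which will allocate the participant to either the EG or the CG (single-blind allocation", and Figure 1 is not reproduced. It is also true that having no sham workshop reveals the arm for certain only once sessions start, which is after baseline. This stands as a limit: knowledge of the arm at baseline is an inference. It is a strong one, since the envelope is used at assignment, concealment lasts only until then, and no blinding of participants is claimed.

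Other stronger readings are tempting but not supported:

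- **That any baseline reaction passes in full into the effect.** Only the part that has gone by follow-up does. Participants know their arm throughout follow-up, so some persistence is plausible.
- **That the direction is known.** Nothing in the document fixes the sign, so the effect could be overstated or understated.
- **That the larger expected loss in controls arises here.** The 20% and 40% in Sample size calculation are overall planning rates, and none of that loss is assigned to the gap between envelope and baseline. Reordering would not stop a disappointed control from leaving. It would mean that this person has a baseline record.
- **That reordering protects assessor blinding throughout.** It helps at the first visit only. Participants know their arm at both follow-ups under any order.
- **That all outcomes are equally exposed.** The trial is sized on the RBMT-3, a performance test given by trained, blinded assessors. The self-ratings are the weaker point.

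Finally, the article also describes effect measures at each follow-up in terms that could mean a simple between-group difference, which a transient baseline shift would not touch. But the main efficacy analysis is the mixed model with the interaction, so the exposure remains.

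**Conclusion.** The point holds in limited form. The article states outright that baseline follows randomisation, and no safeguard keeps participants unaware of their arm at that visit. No later analysis plan can turn these scores into pre-randomisation measurements. The planned interaction is biased by exactly the part of any between-arm reaction that is present at baseline and absent at follow-up. The size and sign are unknown, and the values of 0.42 and 1.0 are illustrations. The conclusion rests on two assumptions: that participants learn their arm before baseline, and that the group-by-time term is the efficacy contrast. Both are the natural reading, but neither is spelled out. The loss of people between allocation and baseline is a real gap of undocumented extent.

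**What to change.** In the description of the baseline and follow-up assessments, replace the statement that baseline follows randomisation with one that it precedes it. The order becomes: screening and consent, baseline assessment by the psychologist, then opening of the envelope by centre staff other than the assessor. The allocation paragraph and the flowchart need the same change. If the envelope is in practice already kept closed until baseline is complete, the text should say so.

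The cost is a small amendment. Workshops already start only after baseline, and screening is done by a physician or nurse rather than by the psychologist, so no visit, test or participant is added. The downsides are that participants learn their allocation slightly later and that eligible people who do not attend baseline are not randomised. The second also reduces loss after randomisation, and it gives everyone randomised a baseline score on which early leavers can be compared by arm.

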### Description of the intervention

Once the baseline assessment has been conducted, individuals in the EG will start the multifactorial intervention. The memory training workshop is designed to stop or delay age-related memory losses and promote personal autonomy, thus enhancing mental and physical wellbeing. Specifically, these workshops aim to broaden knowledge on memory function, improve memory processes, and increase self-esteem and quality of life by providing some strategies (i.e., strategies for collecting and coding information) and relational space. The intervention will consist of twelve 90-minute group sessions provided once a week by a psychologist specialized in memory training. The groups will be composed of around 15 people. Each session will have its own objectives, materials, and activities (Table 2). The content of the intervention is based on memory training from different perspectives such as cognitive and emotional aspects and social and individual skills.

**Table 2 Tab2:** Contents of the memory training workshop by session

SESSION	CONTENT
1	Presentation of the workshop: Objectives and Methodology
2	Types of memory I: Explanation of the different types of memory and their role in normal life
3	Types of memory IIa: Strategies for gathering and codifying information.
4	Types of memory IIb: Strategies for selecting and storing information.
5	Types of memory III: Strategies for gathering, codifying, selecting, storing and retrieving information. Importance of the context and the meaning of things. Semantic and episodic memory.
6	Types of memory IV: Strategies for gathering, codifying, selecting, storing and retrieving information. Individual differences.
7	Types of memory V: Strategies for retrieval according to individual profile. Improving self-esteem.
8	Types of memory VI: Strategies for recovering social skills.
9	Personal and social skills
10	New contexts and opportunities. Conceptual maps (physical and mental).
11	Evaluation of the workshop.

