## Methods

### Study design

This is a randomized controlled trial, comparing a group of individuals taking part in the memory training workshops (EG) with another group with similar characteristics not attending the workshops (CG). Data will be collected at baseline and at 3 and 6 months.

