### Sample size calculation

The sample size was calculated to detect a difference in everyday memory higher than 2 points (0.5 SD) on the mean RBMT-3 score between the control and the intervention group [32]. Accepting an alpha risk of 0.05 and a beta risk of 0.1 in a bilateral contrast, and assuming a mean score of 16.07 and an SD of 4.19 [33] on the RBMT-3 in the Spanish population aged between 70 and 75 years, 75 individuals in each group will be needed. To ensure this sample size and considering an estimated rate of losses of 20 % in the EG and 40 % in the CG, the final sample size needed is 195 individuals (90 in EG and 105 people in CG, respectively).

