### Statistical analysis

Baseline comparability between the study arms will be assessed through bivariate analyses of the pre-test data set group (dependent and independent variables) comparing the control and the experimental arms. The chi-square test will be used to compare qualitative data, as well as the Student *t* test or the Mann–Whitney test for quantitative data, depending on the normality of the distribution. If differences are found in baseline characteristics, we will consider adjusting for these variables in the efficacy analysis.

A descriptive analysis will be conducted for results at baseline, at the immediate follow-up and at the delayed follow-up for the EG and CG. Categorical outcomes will be described through raw frequencies or percentages, and continuous outcomes will be described through mean scores and standard deviations. Effect measures for each outcome at the immediate and delayed follow-ups will be computed as the mean of the differences of the aggregated scores for the EG and CG. Effect measures will be presented with their 95 % confidence intervals.

The main statistical analyses to assess the efficacy of the intervention on self-perceived memory, everyday memory and executive control abilities will be performed using a repeated-measures mixed effects model for each main outcome defined in the protocol [34]. In each model, the independent variables will be the group (EG or CG), time (baseline, immediate follow-up or delayed follow-up) and any relevant characteristics that differ between the groups at the baseline assessment (e.g., age or educational level). An interaction term between time and group will be included in the analyses. The models will be fitted with the available data, ignoring missing data.

To determine whether the results have been influenced by missing data, we will conduct sensitivity analyses by fitting the models with completed datasets obtained by imputing the missing data [35]. In this analysis, missing values for the immediate or delayed post-test assessments will be imputed through the Last Observation Carried Forward (LOCF) strategy. According to this strategy, missing values will receive the value obtained by the participant in the previous assessment. In addition, we will perform sensitivity analyses restricted to those participants attending at least 80 % of the sessions.

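### Workshop groups of about 15 exist in one arm only, and neither the sample size nor the listed model terms allow for correlation within them; if there is any, precision and power are overstated

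*Protocol article*

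**What the plan says.** Allocation is by individual. The text under Figure 1 says of each eligible participant that "he or she will be randomly assigned to the EG or to the CG using a closed, opaque envelope".

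Only the EG is then grouped. Description of the intervention states: "The intervention will consist of twelve 90-minute group sessions provided once a week by a psychologist specialized in memory training", and adds: "The groups will be composed of around 15 people". Under Study design, the EG is compared "with another group with similar characteristics not attending the workshops (CG"), so controls belong to no workshop.

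Sample size calculation aims "to detect a difference in everyday memory higher than 2 points (0.5 SD) on the mean RBMT-3 score", with the error rates given as "Accepting an alpha risk of 0.05 and a beta risk of 0.1 in a bilateral contrast", and concludes that "75 individuals in each group will be needed". Its other inputs are an SD of 4.19 and losses of 20% (EG) and 40% (CG), which lead to 90 and 105 enrolled. No ICC or design effect appears.

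Statistical analysis specifies a repeated-measures mixed effects model: "In each model, the independent variables will be the group (EG or CG), time (baseline, immediate follow-up or delayed follow-up"), plus baseline characteristics that differ and a time-by-group interaction. No term for workshop group is listed. The two sensitivity analyses (LOCF imputation, and restriction to those attending at least 80% of sessions) do not address it, and Strengths and limitations does not mention it.

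**The concern.** EG members share a psychologist, sessions and peers for twelve weeks, while controls share nothing comparable. The article itself describes routes by which members of one workshop could come to resemble each other: it works on social skills and self-esteem, has staff evaluate the progress of each group as well as each person, and names social contact as a possible benefit. Two of the main outcome measures are self-perceived memory scores, which such influences could well affect.

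A repeated-measures model deals with correlation between visits of the same person. It does not, by that fact, deal with correlation between different people in the same workshop. Using change from baseline does not remove it either. Baseline is taken before the workshop starts, so any workshop-level effect arises later and sits inside the change.

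If such correlation exists and is ignored, the variance of the EG mean is understated. The reported intervals are then too narrow and the real power is below the planned figure. When the average effect is zero but workshop groups differ, false positives exceed 5%.

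**Working it through.** **Inputs from the protocol article.** SD 4.19, difference 2 points, two-sided alpha 0.05, beta 0.1, 75 per group, losses of 20% and 40%, enrolment of 90 EG and 105 CG (Sample size calculation); workshop groups of about 15 (Description of the intervention).

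**Assumed, because the document gives no value.** Workshop-level ICC ρ from 0 to 0.10, equal group sizes, and losses spread evenly over groups.

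**Step 1: the plan's own figure.** n per group = 2 × [SD × (z for alpha + z for power) / difference]².
- Two-sided: 2 × [4.19 × (1.9600 + 1.2816) / 2]² = 92.2, so 93 rather than 75.
- One-sided: 2 × [4.19 × (1.6449 + 1.2816) / 2]² = 75.2, which is close to the stated 75.

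Neither version contains a clustering component, so the stated 75 holds no hidden margin for it.

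**Step 2: numbers analysed.** Enrolment is 75 × 1.2 = 90 and 75 × 1.4 = 105. After the stated losses, 90 × 0.8 = 72 EG and 105 × 0.6 = 63 CG remain. The EG forms 90 / 15 = 6 workshop groups, with 72 / 6 = 12 retained in each.

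**Step 3: formulas for a partially nested comparison at one time point.**
- EG design effect: DE = 1 + (12 − 1)ρ
- True SE = 4.19 × √(DE/72 + 1/63); the unadjusted SE sets DE = 1
- R = true SE / unadjusted SE
- Type I error of the unadjusted test = 2 × [1 − Φ(1.96 / R)]
- Power for 2 points with the correct SE = Φ(2 / true SE − 1.96)

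At ρ = 0: SE = 4.19 × √(1/72 + 1/63) = 0.723, and power = Φ(0.807) = 79%.

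At ρ = 0.05: DE = 1.55 and SE = 4.19 × √(1.55/72 + 1/63) = 0.810, so R = 1.121. Type I error = 2 × [1 − Φ(1.748)] = 8.0%, and power = Φ(0.508) = 69%. The true SE is 12% larger than the unadjusted one; equivalently, the unadjusted SE is 1 − 1/1.121 = 11% too small.

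| ICC | DE (EG) | R | Type I error | Power, 2 points |
|---|---|---|---|---|
| 0 | 1.00 | 1.000 | 5.0% | 79% |
| 0.01 | 1.11 | 1.025 | 5.6% | 77% |
| 0.02 | 1.22 | 1.050 | 6.2% | 75% |
| 0.05 | 1.55 | 1.121 | 8.0% | 69% |
| 0.10 | 2.10 | 1.230 | 11.1% | 61% |

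**Step 4: check by simulation.** An unadjusted t test on six groups of 12 against 63 controls (20,000 trials) rejected in 6.2%, 8.0% and 11.4% at ICC 0.02, 0.05 and 0.10. With 75 per arm and groups of 12 to 13, the formula gives 5.7%, 6.3%, 8.4% and 11.8% at the four positive ICCs; 40,000 simulated trials per value gave 5.7%, 6.2%, 8.5% and 11.9%.

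**Step 5: what belongs to clustering.** The fall from 90% to 79% does not. Using 75 instead of 93 brings two-sided power to 83%, and the way losses were added (leaving 72 and 63) brings it to 79%. Only the steps below 79% come from clustering. They do not yet include the loss of degrees of freedom that goes with about six clusters.

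**The case against.** Several points on the other side are fair.

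- **The excess is conditional.** A reader might infer that the standard errors are too small and that the 5% level is exceeded. The document does not support that as a flat statement: it gives no ICC, at ICC 0 there is no excess, and at 0.01 it is slight. This stands.
- **The type I figures need real differences between workshop groups.** Participants are randomised individually. If the workshop changed nobody, training together would create no EG-only correlation, and likeness among people from one health centre is present in both arms. The inflated error rates apply when the average effect is zero but workshops differ. If the workshop works on average, the harm lies in interval width and power. This stands.
- **The model may contain a workshop effect after all.** A reader might infer that EG participants are definitely treated as independent. Statistical analysis lists independent variables, that is, fixed terms, and names no random effects at all, not even one for participant. A workshop effect in an analysis plan that is not shown cannot be ruled out. This weakens the modelling half. It does not touch the sample size, whose inputs are set out without any allowance, and a later analysis plan cannot restore power.
- **The calculation is not the planned model.** It is a two-sample comparison at one visit. For the group-by-time contrast, the relevant ICC is that of change from baseline, which may be smaller or larger. This stands as a limit on the figures, not on their direction.
- **Delivery is standardised.** The Quality control section relies on trained staff and common materials. That may reduce differences between leaders; it does not remove peer effects.
- **The Abstract gives a total of 230, not 195.** A reader might take the difference as a reserve for clustering. No reason is given for it, so it cannot be read that way. It does make the number of workshop groups uncertain. At the same group size and arm ratio, R and the type I error would not change; power would be somewhat higher.

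**Conclusion.** The point holds in conditional form. The design is partially nested, the sample size makes no allowance for it, and the model terms that the article lists include none. For any positive workshop-level ICC, following the text as written understates the EG variance.

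How much is unknown. Over the assumed ICC range of 0.01 to 0.10, with six groups of 12 and 63 controls, the true SE is about 2.5% to 23% larger than the unadjusted one, and clustering costs between 2 and 18 percentage points of power. The direction is firm. The size depends on the ICC, on the group numbers derived from the 195 total, and on a one-visit approximation. This is a worthwhile correction at low cost, not proof that the planned test is invalid.

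**What to change.** 1. **Data.** Record the workshop group of every EG participant. Without this identifier the adjustment may be impossible later.
2. **Statistical analysis.** Include a random workshop-group effect for the EG only, with each control as a singleton, and use Satterthwaite or Kenward-Roger degrees of freedom. For the group-by-time contrast, the effect has to act on change from baseline.
3. **Sample size calculation.** State the power over a range of ICCs, such as the one tabulated above, with the range labelled as an assumption. This does not require enrolling more people.

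The cost is one variable in the dataset and a few sentences of text. The price at analysis is wider intervals and a cluster variance estimated imprecisely from about six groups. For that reason, an analysis without the workshop term could be reported alongside, so that readers can see how much the adjustment matters.
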